#### Data accuracy

Data from the baseline street surveys were entered by one data entry clerk. In order to assess the accuracy of data entry, a randomly selected sample of 5% were double checked by Project staff. An agreement level of 90% or better was determined as acceptable.

### Statistical analyses

In the available ED and police data concerning violence, it is not possible to determine whether multiple incidents on the same day are related or not: it is feasible that a single episode involving violence can lead to multiple arrests and/or injuries requiring hospital treatment. Furthermore, as the primary interest is premises-level risks it is reasonable to assume that premises failings persist across a session and therefore that multiple incidents in one session can be assumed as partly reflecting those risks. For violence, therefore, we assumed that one or more violent incidents indicated that for that session the premises was in a state of failure and was thus coded as a binary event. Furthermore, it is likely that any intervention effect will wane over time, particularly as premises are usually subject to high staff turnover rates. Moreover, for any definitive trial it is feasible that numerous external factors might influence premises-level failure rates, such as sporting events and temporary closure. While Poisson models can accommodate aggregate count data and would normally be suitable, in order to account for potential intervention wane, time varying covariates, censoring, multiple events and discontinuous risk intervals, the preferred approach was to develop an Andersen-Gill model [21], a derivation of the Cox proportional hazards model [22,23]. The individual level BrAC data are clustered in premises and location and is available pre- and post-intervention. This suggests that a multilevel mixed-effects linear regression [24] is appropriate from which design effects and intra-cluster correlation coefficients for BrAC and the other survey measures can be calculated.

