A range of outcome measures have been used in premises-level evaluations, including police records, rates of hospital treatment following violent injury and customer breath alcohol concentration as well as subjective ratings such as customer self-report and observations of disorder and intoxication by research staff. While convenient, subjective ratings can be susceptible to response and reporting biases. Police records follow a standardised recording protocol, especially after the implementation of a national crime recording standard in England and Wales, that makes them more reliable and appropriate for studying changes in crime over time. As these data also contain information on the location of incidents they can be linked to individual premises. However, police data are susceptible to systematic bias as usually only those incidents that are reported to the police or occur when the police are present are recorded. Emergency Department (ED) data are not susceptible to such biases as serious injury will require hospital treatment irrespective of where and when the assault took place. However, this does mean that ED data are biased towards more serious assaults. ED data are usually collected by reception staff who record details of violence location, time, day and weapon. If the patient declares that their injury is assault-related then this prompts a series of questions about the nature of the incident [11]. In respect of premises proclivity to sell alcohol inappropriately, customer intoxication can be assessed using subjective measures but are inferior to objectively recorded Breath Alcohol Concentration (BrAC) collected using alcometers [12-14].

Of the existing evaluations of premises-level interventions, only three have used a RCT design to measure intervention effectiveness in terms of objectively measured outcomes of intoxication [15,16] or disorder [9]. Furthermore, when matching procedures were used for these studies, they were limited to "bar type" or premises size and failed to consider the past history of alcohol-related harm and opening hours - characteristics that may also predict levels of violence and intoxication. Moreover, past trials have failed to account for the displacement or diffusion effects of premises-level interventions which may undermine evaluations of intervention effectiveness.

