### Inclusion/exclusion criteria

Premises were eligible for inclusion if (1) a police-recorded violent offence took place in or immediately outside the premises in the twelve months before recruitment, (2) or an attendance at an ED for violent injury was associated with the premises or (3) the premises was identified as being at high risk of disorder by the local police licensing officer. It is likely that police records represent a conservative estimate of the number of serious violent incidents in and around the target premises as it has been demonstrated that the majority of serious violent incidents are not reported to the police [17], but police data are likely to reflect information on incidents where no ED attendance is required, suggesting that a composite dataset is appropriate.

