### Matching

The unit of allocation was the individual licensed premises, stratified by risk of harm and area. A risk index was calculated for each licensed premises using the formula Risk = P/(T*C) where P is the number of police recorded incidents in the twelve months preceding project start, T is the number of hours open after 11 pm on Friday and Saturday night and C is the maximum premises capacity. Matching was incorporated into the study to reduce possible imbalances between treatment arms expected with a small sample size, but was not accounted for in subsequent analyses due to the loss of degrees of freedom [18].

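### The violence analysis states no use of each premises' own pre-trial police record, a value the trial already holds; one covariate could make the hazard ratio more precise at a cost of one degree of freedom

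*Protocol article*

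**What the plan says.** All places are in the protocol article.

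- **Statistical analyses, violence.** Each session is coded as failed or not, and "the preferred approach was to develop an Andersen-Gill model [21], a derivation of the Cox proportional hazards model". The model was chosen "in order to account for potential intervention wane, time varying covariates, censoring, multiple events and discontinuous risk intervals". Prior failure rate is not among these reasons, and no covariate list is given.
- **Statistical analyses, breath alcohol.** Here the two time points are mentioned: "The individual level BrAC data are clustered in premises and location and is available pre- and post-intervention". Nothing equivalent is said for violence, although the Measures section says the same outcome measures were taken at baseline and at three months.
- **Matching.** The risk index is P/(T × C), where "P is the number of police recorded incidents in the twelve months preceding project start", T is late opening hours and C is capacity. Matching was used to limit imbalance "but was not accounted for in subsequent analyses due to the loss of degrees of freedom".
- **Background.** Matching in earlier randomised trials is criticised because it "failed to consider the past history of alcohol-related harm and opening hours - characteristics that may also predict levels of violence and intoxication".
- **Inclusion/exclusion criteria.** Police-recorded violence "in the twelve months before recruitment" is one of three routes to eligibility. The others are an associated emergency department attendance and the licensing officer's judgement.

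**The concern.** Licensed premises are likely to differ in how often they fail. With 32 premises and a three-month follow-up, such differences can make up much of the uncertainty in the hazard ratio. A premises' own recent record is the natural variable to absorb them, and the trial holds it.

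Matching is the only stated route by which that record could reach the violence analysis, and the article closes it. The reason given, degrees of freedom, applies to a set of pair terms. It does not apply to a single baseline covariate.

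What is at stake is the width of the interval, and how well the trial can tell a definitive study how much between-premises variation remains once history is known. The article lists information on design parameters among its aims.

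**Working it through.** **1. Degrees of freedom.** There are 32 premises (6 + 10 + 8 + 6 + 2) in 16 pairs. A two-arm comparison leaves 32 − 2 = 30. Pair terms cost 16 − 1 = 15, leaving 15. One covariate costs 1, leaving 29.

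**2. The plan's only figure on precision.** The Sample size section gives 80% power for 16 pairs at 0.8 SD, two-sided 5%.
- Analysed unpaired, as the Matching section implies: 0.8 × √(16/2) − 1.96 = 2.263 − 1.960 = 0.303, so power is 61.9% (59.1% with the t distribution). The 80% is not reproduced.
- Analysed as pairs, with 0.8 taken in units of the SD of within-pair differences: 84.8% (t).

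The power statement is a separate matter and serves here only as a scale. A baseline covariate with correlation r to the outcome multiplies the standard error by √(1 − r²). The documents give no r, so a range is shown:

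| r (assumed) | SE multiplier | Power, z | Power, t on 29 df |
|---|---|---|---|
| 0 (no covariate) | 1.00 | 62% | 59% |
| 0.3 | 0.95 | 66% | 63% |
| 0.5 | 0.87 | 74% | 71% |
| 0.7 | 0.71 | 89% | 86% |

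**3. Simulation closer to the planned model.** The recurrent-event model was simulated in its constant-hazard form (a Poisson rate model) with robust variance by premises. Inputs from the article are 32 premises, 1:1 allocation within pairs matched on the index, and three months of follow-up. Assumed inputs are the yearly failure rate, the between-premises coefficient of variation (CV), a hazard ratio of 0.8, and the correlation of each premises' underlying rate between baseline and follow-up (persistence). The covariate is log(P + 0.5). The variance cut is 1 − (adjusted SD / unadjusted SD)².

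| Rate, CV, persistence | SD of log HR, unadjusted → adjusted | Variance cut | Mean robust SE, unadjusted → adjusted |
|---|---|---|---|
| 20, 1.0, 0.9 | 0.327 → 0.254 | 40% | 0.357 → 0.232 |
| 10, 0.8, 1.0 | 0.316 → 0.266 | 29% | 0.354 → 0.261 |
| 10, 0.8, 0.7 | 0.357 → 0.336 | 11% | 0.352 → 0.313 |
| 4, 0.8, 1.0 | 0.476 → 0.450 | 11% | 0.468 → 0.414 |
| 10, 0.4, 0.7 | 0.294 → 0.293 | 1% | 0.277 → 0.269 |

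The mean log hazard ratio moved by at most 0.012 (−0.233 to −0.221, against a true −0.223), so adjustment does not shift the estimate materially.

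**4. Upper end and persistence.** With a hazard ratio of 0.5 and full persistence, the SD fell from 0.421 to 0.399 (6 failures a year, CV 0.6), 0.321 to 0.276 (12, 0.6), 0.382 to 0.284 (12, 1.0) and 0.329 to 0.196 (24, 1.0). These are variance cuts of 10%, 26%, 45% and 65%. A repeat of these four settings gave 8% to 58%. At persistence 0.7 the cut fell to about 0–21%, and at 0.4 to about zero.

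**5. Does matching already do the job?** The modelled hazard is per premises, while the index divides by hours and capacity. A large venue with many incidents and a small one with few can share an index. In row 2 of the step 3 table, adjustment still helps after matching on the index.

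Ignoring the matching also tends to leave the reported standard error too large when history is strongly prognostic: 0.357/0.327 = 1.09 and 0.354/0.316 = 1.12 in the first two rows. In the other three rows there is no inflation (0.99, 0.98, 0.94).

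After adjustment the robust SE is slightly too small: 0.232/0.254 = 0.91 in row 1 and 0.261/0.266 = 0.98 in row 2. The SD columns are therefore the fairer measure of gain.

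**The case against.** The strongest reply is that this is silence in a condensed article. No covariates are listed for the violence model, and such a list is commonly left to an analysis plan. What the article explicitly leaves out is the matching; nowhere does it exclude baseline violence as a covariate. An Andersen-Gill model could take prior count as a covariate, or pre-intervention sessions as risk time. This stands. A reader might infer that the trial makes no use of violence history, or has decided against adjustment, and the text supports neither. History helps set eligibility and enters the matching within towns, which limits chance imbalance.

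A reader might also infer that the trial asserts that history predicts violence. The Background says only that it may.

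The reply also rightly says that the size is not the trial's own. Rates, heterogeneity and hazard ratios are all assumed. The largest gains need rates that persist fully, whereas the article itself points to high staff turnover. The trial is exploratory, and the Sample size section says a significant effect was not anticipated.

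What the reply does not meet is the stated reasoning. The article drops the one declared use of history in the analysis, for a cost that a single covariate does not carry, and describes nothing in its place.

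**Conclusion.** The point holds as a nearly free gain in precision that the described analysis does not claim. It is not an error that invalidates the analysis, and it is not a bias.

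The cut in the true variance of the log hazard ratio runs from about none to roughly 60%. The low end applies when failures are few, premises differ little, or their rates do not persist. The high end needs about 24 failures per premises-year, a CV of 1.0 and full persistence. The simulations also assume a constant hazard and log-normal heterogeneity, and those in the step 3 table match across all 32 premises rather than within town.

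It is tempting to quote a power gain, for example 58% to 71% for a hazard ratio of 0.5 at 12 failures a year and CV 0.6: Φ(0.693/0.321 − 1.96) and Φ(0.693/0.276 − 1.96). The documents do not support this as a property of the trial. The effect, the rates and full persistence are all assumed, and no stated decision turns on that power.

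**What to change.** State the following before outcomes are analysed by arm:

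- Include log(police failure sessions in the 12 months before randomisation + 0.5) as one fixed covariate in the Andersen-Gill model. Code sessions as for the outcome. The 0.5 is needed because premises admitted through the other two eligibility routes may have no police-recorded incident.
- Use robust variance clustered by premises, preferably with a small-sample correction given 32 clusters.
- Report the unadjusted hazard ratio beside the adjusted one.

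One count window for all premises, ending just before randomisation, would be tidiest. P runs to project start, eligibility runs to recruitment, and randomisation waited for all 32 audits and action plans. If no refreshed police extract is available, the P already held will do.

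The cost is one sentence of analysis wording, one degree of freedom and at most one further police extract. No new data collection is needed.

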**Objective:**

To describe the research design for an exploratory trial examining the feasibility and acceptability of a premises-level intervention designed to reduce severe intoxication and related disorder. The study also aims to assess the feasibility of a potential future large scale effectiveness trial and provide information on key trial design parameters including inclusion criteria, premises recruitment methods, strategies to implement the intervention and trial design, outcome measures, data collection methods and intra-cluster correlations.

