**Design:**

A randomised controlled trial in licensed premises that had experienced at least one assault in the year preceding the intervention, documented in police or hospital Emergency Department (ED) records. Premises were recruited from four study areas by piloting four recruitment strategies of varying intensity. Thirty two licensed premises were grouped into matched pairs to reduce potential bias and randomly allocated to the control or intervention condition. The study included a nested process evaluation to provide information on intervention acceptability and implementation. Outcome measures included police-recorded violent incidents, assault-related attendances at each premises' local ED and patron Breath Alcohol Concentration assessed on exiting and entering study premises.

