### Measures

The outcome measures used in the study were selected for their appropriateness and objectivity in identifying and accurately associating violence, severe intoxication and environmental disorder with study premises. Identical outcome measures were used at baseline and at the three month follow-up to measure violence, severe intoxication and environmental disorder.

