#### Street observations, surveys and breath alcohol concentration data

A surveyor standing four to five metres from the main entrance to a premises carried out environmental observations for the duration of the data collection episode. This involved the continuous observation of pedestrians moving to and from the study premises, a spot survey of environmental conditions every 30 minutes and recording and describing any disorderly or violent incident in the immediate area, such as ejections, fights and arrests. A second pair of surveyors recruited every seventh individual walking past a designated point near to the study premises and asked them to take part in a survey. If the person assented then the surveyor proceeded to ask the survey questions. All survey responses were completed by the surveyors on behalf of the respondents. On completion, respondents were asked to provide a BrAC reading using the alcometer. This was recorded. Once the respondent had left the vicinity, the surveyor rated them on the four descriptors used to identify drunkenness: gait, eyes and speech [14] and overall drunkenness along a 10-point Likert scale. All potential respondents who did not agree to participate were scored on the same subjective descriptors so that potential sampling biases could be assessed.

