### Sample size

Sixteen pairs of premises provide 80% power to detect a 0.8 standard deviation difference in premises-level rates of intoxication and violence using a two-tailed alpha of 0.05. The study was an exploratory trial and a significant effect was not anticipated.

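### Severe intoxication is the target, but the stated BrAC analysis models the mean and yields neither a rate of severe intoxication nor its ICC

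*Protocol article*

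**What the plan says.** All references are to the protocol article.

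- **Abstract, Objective:** the trial concerns "a premises-level intervention designed to reduce severe intoxication and related disorder". Outcome measures and intra-cluster correlations are listed among the design parameters it should supply.
- **Measures:** the same measures are taken at baseline and three months "to measure violence, severe intoxication and environmental disorder".
- **Sample size:** "Sixteen pairs of premises provide 80% power to detect a 0.8 standard deviation difference in premises-level rates of intoxication and violence".
- **Statistical analyses:** BrAC readings are clustered and available before and after the intervention. "This suggests that a multilevel mixed-effects linear regression [24] is appropriate". The same model is meant to supply the ICCs and design effects, both for BrAC and for the remaining survey items.
- **Street observations, surveys and breath alcohol concentration data:** surveyors "recruited every seventh individual walking past a designated point near to the study premises". The Abstract describes the outcome as "patron Breath Alcohol Concentration assessed on exiting and entering study premises".

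The article gives no BrAC cut-off that defines severe intoxication.

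**The concern.** Severe intoxication is an upper-tail quantity: the share of people above some level. A linear model of BrAC estimates a difference in means, which is neither that share nor a rate of any kind. The article makes this step explicitly for violence, where a session with one or more incidents is defined as a failure and the choice is justified. It makes no such step for intoxication. The reason given for the BrAC model (clustered data before and after the intervention) supports a multilevel model, but does not make the mean the right summary for severe intoxication.

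Two things are at stake. First, a definitive trial powered on severe intoxication needs a control-arm event rate and an ICC for that binary outcome, and the stated model supplies neither. This follows from the text and needs no power assumption. Second, if the intervention acts mainly on the most intoxicated patrons, a comparison of means may miss a change that a threshold analysis would be more likely to show.

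**Working it through.** **1. The article's own figure.** The inputs are 16 pairs, 0.8 SD and two-sided alpha 0.05. Read as a paired t-test with 0.8 in units of the SD of within-pair differences, the noncentrality is 0.8 × √16 = 3.2 on 15 df, and power is 84.8%. Fifteen pairs give 82.1% and 14 give 79.0%, so 16 pairs for 80% is reproduced closely. An unpaired comparison of 16 with 16 gives 59% to 62%; that is a separate matter. For this point, what counts is that the calculation refers to premises-level rates of intoxication, which a linear model of individual BrAC does not estimate.

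**2. Assumptions for the illustration.** The article gives no BrAC distribution, share severely intoxicated, number of respondents per premises or ICC. Assume normal BrAC with SD 1 in both arms, 16 premises per arm, 30 respondents each (480 per arm), ICC 0.05 for both analyses, and z-tests at two-sided 0.05.

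- Design effect: 1 + 29 × 0.05 = 2.45. Effective n per arm: 480 / 2.45 = 195.9.
- SE of the mean difference: √(2 / 195.9) = 0.101 SD.

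**3. Effect on the mean.** Let a share q be severe, with cut-off z and normal density φ(z). Half of the severe group responds.

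- (a) Responders fall only to the cut-off: shift = 0.5 × (φ − qz). For q = 0.10: 0.5 × (0.1755 − 0.1282) = 0.024 SD.
- (b) Responders become typical non-severe patrons: shift = 0.5 × φ / (1 − q). For q = 0.10: 0.5 × 0.1755 / 0.9 = 0.097 SD.
- (c) The whole distribution shifts until prevalence is halved: shift = z(q/2) − z(q). For q = 0.10: 1.645 − 1.282 = 0.363 SD.

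**4. Effect on the proportion.** For q = 0.10, prevalence falls from 10% to 5% in all three cases. SE = √((0.09 + 0.0475) / 195.9) = 0.0265, so z = 0.05 / 0.0265 = 1.89 and power is 47%.

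**5. Power under each scenario.**

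| Share severe, halved | Mean, (a) | Mean, (b) | Mean, (c) | Proportion, any of (a)–(c) |
|---|---|---|---|---|
| 5% | 5% | 8% | 88% | 26% |
| 10% | 6% | 16% | 95% | 47% |
| 20% | 9% | 41% | 99% | 80% |
| 30% | 16% | 69% | over 99% | 95% |

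A gamma-shaped BrAC distribution, with the SD allowed to shrink after the intervention, raises the mean's power somewhat: to 25% for (b) at 10% severe and to 81% for (b) at 30% severe, where the shift is 0.26 SD. At ICC 0.02 (design effect 1.58, effective n 303.8), the 10% row becomes 6%, 23%, 99% and 65%.

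In every tail-confined scenario the threshold analysis has more power. In every whole-distribution scenario the linear model does.

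**The case against.** The strongest case against the point has five parts.

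- **The target need not be the tail.** The end of the Background and the description of the intervention speak of intoxication without the word severe. An audit covering staff, environment and procedures could shift the whole distribution. This stands: column (c) shows the linear model doing better in that case.
- **The linear model is not an error.** It is standard for a continuous clustered measurement. This stands, and it is why the model should be kept.
- **A fuller plan may contain a cut-off.** This stands in part. One cannot say from a condensed article that the linear model is the only BrAC analysis. What can be said is that the analysis the article does state does not match the outcome and the rates it names.
- **The trial is exploratory and no significant effect was expected.** This weakens the power argument. It does not weaken the argument about design parameters, which are the purpose of an exploratory trial.
- **Individual readings are kept, so a rate and ICC could be derived later.** This stands: nothing is lost for good. A cut-off chosen after the results are known is less credible, however.

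A reader might infer that the linear model is nearly blind to a reduction in severe intoxication. The documents do not support that. It needs a small severe group whose readings fall only as far as the cut-off. Nor does the sampling of passers-by, entrants and light drinkers favour one analysis over the other, because it dilutes the mean and the proportion alike.

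**Conclusion.** The point holds as a mismatch between the named outcome and the stated analysis. The text supports this directly: severe intoxication and rates of intoxication are named, while a model of mean BrAC is stated. Neither an event rate nor an ICC for severe intoxication follows from that model.

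The loss of power is possible but not established. Across tail-confined scenarios at ICC 0.05, power for the mean runs from about 5% to 81%, against 26% to 95% for the proportion. A shift of the whole distribution reverses the order. These figures rest on assumed values for distribution, prevalence, respondents per premises and ICC. It would go too far to conclude that a working intervention would be reported as ineffective.

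The recommendation does not depend on the shape of the effect, because it adds to the linear model and does not replace it. It is a cheap improvement.

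**What to change.** Keep the multilevel linear model of BrAC. Add a mixed-effects logistic model, with the same fixed and random effects, for BrAC above a cut-off fixed before allocation is revealed. The cut-off could be a recognised threshold or a percentile of pooled baseline BrAC, with a second cut-off as a sensitivity check. Name this as the analysis of severe intoxication, and report its control-arm rate and ICC as design parameters alongside those for mean BrAC.

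No new data are needed. The cost is one more analysis to report and a somewhat arbitrary cut-off; fixing it in advance and showing a second one limits selective choice.
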